**Fig 2 pone.0329643.g002:**
[figure not shown]
Sample size analysis. Includes a range of parameters. The “Sensitivity priors” represents the approximate expected sensitivity of our method, and the “proportion positive” represents the proportion of samples that will contain an organism, which also means that should test positive.

Constrained resources (e.g., funding), demands a higher pre-test probability at the time of testing to estimate with confidence. For example, if we only have funding for 40 persons tested, we will elect to test persons with clear known linkages to a person with the illness (symptomatic family member of someone diagnosed with norovirus), or we would perform clearance testing in persons with known disease using these methods (the guidelines call for clearance testing for a variety of illnesses). With greater funding, testing can approximate normal clinical encounters and have less restrictive criteria for testing. If the funding is limited to 40 samples, we will endeavour to control the testing method, aiming for in-clinic self-testing.

### Recruitment

The recruitment strategy will be multifaceted to obtain samples from a range of representative clinical settings, e.g., outbreaks, community, and in-hospital. The strategy will involve a central study coordinator supporting acquisition of samples, coordinating the multiple sources. For outbreaks, the study coordinator will be able to send sample collection packs to the patient, family, and/or symptomatic members of an outbreak via express post. In community settings, the study coordinator can obtain samples from GP practices that are seeing patients who were recently inpatients in hospital – identified from admission lists, or our Infectious Diseases Physician study collaborators. Inpatients, especially those which represent persons with a high pre-test probability, will be identified, recruited via their treating practitioner, and then consented to take part in the study. Consent will be performed verbally over the phone by a study coordinator (records kept locally), and/or with a physical form sent in a return envelope.

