### Timeline

Participant recruitment is expected to commence in early 2025. Recruitment and data collection are expected to be completed within two years. Results are expected shortly after, placing the trial completion date in late 2027 or early 2028. It is expected that an average of 3–6 swabs will be obtained per week across collection sites. Some situations, such as outbreaks or mass gathering events, will allow for greater numbers of swabs to be collected in a small timeframe. After participants return the test samples, they will receive a follow-up phone call. Results of the bulk faeces test will be returned to the patient by the clinician that requested the test.

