### Sample size calculation

A sample size analysis with a wide range of input parameters, as described by Hajian-Tilaki 2014, demonstrates that less than 600 samples will be sufficient to cover a range of diseases (Fig 2) [16]. Assuming that 30% of samples will contain an organism (“proportion positive”) with an expected sensitivity of at least 95% (“sensitivity priors”) means we will require a sample size of no more than 61 paired samples. As the prevalence of disease in samples decreases, the sample size required is higher. For a sensitivity of 95% and a prevalence of 20%, the sample size increases from 61 to 92. These estimates are based on general sensitivity assumptions and a simplified disease prevalence model, with the literature reporting non-specific prevalence to be approximately 25%, and sensitivity estimates typically >90% [17–20]. These estimates may change slightly as recruitment progresses and the distribution of pathogens becomes clearer. To address potential variability across different pathogens, stratified analyses will be conducted. Power calculations for key pathogen subgroups indicate that, for a sensitivity of 95% (with a range of 90–99%), a minimum of 73 positive samples is required per pathogen subgroup.

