### Statistical methods

We will summarise safety and efficacy data using descriptive statistics, including means, medians, and frequencies. We will use statistical tests to compare groups (e.g., chi-square tests for categorical data, t-tests for continuous data). We will also adjust for multiple comparisons to control for type I error.

Logistic regression models will be used to assess accuracy in the presence of potential confounders. This includes sex (female/male), age (by age group), person collecting sample (self-collect/clinician collect), comorbidities, symptomatology (symptomatic/asymptomatic), duration of symptoms, and whether blood was present in the sample. Subgroup analysis will be conducted according to disease type (e.g., viral, or bacterial).

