#### Primary outcomes.

We will assess the sensitivity, specificity, positive and negative predictive value, and positive and negative agreement value, using 2x2 tables. The gold standard will be bulk faeces PCR testing. Sensitivity is the proportion of individuals with the disease who test positive with rectal swabs. We will assess the cycle threshold (CT) values using general linear models if the relationship is linear as expected and estimate the receiver operating curves and areas under the curve to assess for the potential to need differential CT value cutoffs. All results will be reported using 95% confidence intervals.

The R statistical suite will be used for all analyses and data visualisation. All estimates will be presented with 95% confidence intervals (CI). P-values <0.05 are deemed significant, and p-values <0.1 are considered trends.

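### Several members of one family or outbreak can be enrolled, but the accuracy intervals, regression, sample size and minimum dataset make no provision for clustering, so the 95% intervals may be too narrow

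*Protocol article*

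**What the plan says.** **Recruitment.** Under Study setting, contacts and cases belonging to one outbreak are eligible. Under Recruitment, the coordinator may "send sample collection packs to the patient, family, and/or symptomatic members of an outbreak". Under Timeline, the usual rate is 3–6 swabs a week, but "outbreaks or mass gathering events, will allow for greater numbers of swabs to be collected in a small timeframe". The text after Fig 2 adds an option if funding covers only about 40 people: test people with known links to a case, such as family members, or "we would perform clearance testing in persons with known disease using these methods".

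**Analysis.** Under Primary outcomes, sensitivity and specificity are assessed together with "positive and negative predictive value, and positive and negative agreement value, using 2x2 tables", and "All results will be reported using 95% confidence intervals". Under Statistical methods, "Logistic regression models will be used to assess accuracy in the presence of potential confounders"; those listed are sex, age group, who collected the sample, comorbidities, symptoms and their duration, and blood in the sample. Outbreak, household and site are not among them.

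**Sample size.** "Assuming that 30% of samples will contain an organism" and sensitivity is 95%, "we will require a sample size of no more than 61 paired samples". At 20% positive the figure is 92. Each pathogen subgroup needs 73 positives.

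**Data.** Minimum data requirements lists name, address, date of birth, and recruitment and collection details, but no outbreak or household identifier. Deidentification methods removes names and addresses before analysis.

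**The concern.** People infected in one household or outbreak share the organism, and often the time since onset, the collection route and the laboratory run. Pairs from such people may carry less information than the same number of unrelated pairs. If the intervals come from the 2x2 counts by a simple binomial formula, they take no account of this.

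The measures are not equally exposed:

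- **PPV and NPV** depend on the mix of infected and uninfected people. Infection status clusters in outbreaks, so these measures lose coverage even when swab errors are independent.
- **Sensitivity** conditions on a positive faeces result. It is affected only if swab misses correlate among the positives in one cluster. Specificity behaves the same way with false positives.

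At stake is the lower confidence limit, on which a claim that the swab can replace bulk faeces would rest. With a background rate of 3–6 swabs a week, one large outbreak could supply much of a single pathogen's positives, so the per-pathogen analyses are the most vulnerable.

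**Working it through.** **Step 1: reproduce the plan's sample sizes.** The single-proportion precision formula under independence is n = 1.96² × Se × (1 − Se) / (d² × prevalence). Se = 0.95 and the prevalences are the plan's. The half-width d is not in the text and is inferred here.

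- d = 0.10, prevalence 0.30: 60.82, rounded up to 61 (plan: 61)
- d = 0.10, prevalence 0.20: 91.23, rounded up to 92 (plan: 92)
- d = 0.05, counted in positives: 72.99, rounded up to 73 (plan: 73)

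All three match with no design effect.

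**Step 2: the effect of clustering on sensitivity.** Let m be the number of faeces-positive pairs per cluster and ICC the within-cluster correlation of swab detection among them. Both are assumptions. The design effect is DE = 1 + (m − 1) × ICC, and the effective number of positives is n / DE. As an example, m = 5 and ICC = 0.1 give DE = 1.4, which would turn 61, 92 and 73 into 86, 128 and 103.

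Coverage of a nominal 95% Wilson interval was simulated with beta-binomial clusters, 75 positives and an assumed sensitivity of 90%:

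| Setting | DE | Effective n | Coverage |
|---|---|---|---|
| ICC 0 | 1.0 | 75 | about 95% |
| m = 3, ICC 0.05 | 1.1 | 68 | about 94% |
| m = 5, ICC 0.1 | 1.4 | 54 | about 90% |
| m = 15, ICC 0.1 | 2.4 | 31 | about 80% |
| 25 positives in five clusters of 5, ICC 0.1; 50 sporadic | (25 × 1.4 + 50) / 75 = 1.13 | 66 | about 93% |

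Except in the last row, every positive belongs to a cluster. At m = 15 that means five outbreaks and no sporadic cases. In that setting the lower limit lies above the true sensitivity in about 9% of trials, against about 1.6% under independence.

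**Step 3: PPV and NPV with independent swab errors.** Only infection status is clustered here. Assume 240 pairs, prevalence 30%, and sensitivity and specificity 95%. Then PPV = 0.285 / (0.285 + 0.035) = 0.891 and NPV = 0.665 / (0.665 + 0.015) = 0.978. In this step m counts all pairs in a cluster and the ICC is that of infection.

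- m = 5, ICC 0.3: PPV coverage about 93%
- m = 10, ICC 0.5: PPV coverage about 87%
- m = 20, ICC 0.5: PPV coverage about 79%, NPV about 88%

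At 500 pairs PPV coverage is almost the same, so a larger sample does not cure it.

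**Step 4: could a later analysis plan repair this alone?** Only if the cluster label survives. Address is collected but removed before analysis, and it would not link cases from a shared meal or mass gathering in any event.

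**The case against.** The strongest objection is that this is ordinary statistical analysis plan content. The protocol does not say how the intervals are computed. A 2x2 table gives point estimates, and a bootstrap or robust interval can be built on the same counts. Logistic regression does not exclude a GEE or mixed model. All of this is right: a reader might infer that the plan declares every pair independent, and it does not. What remains is the minimum dataset, which this document does set out, and without an outbreak label a later plan may have nothing to cluster on.

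A reader might also infer from the clearance-testing option that serial samples will bring several pairs from one person. The text does not say so. Clearance testing is one example under limited funding, and repeat pairs are not described. Name, date of birth and the sample's unique identifier would already reveal a repeat participant.

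The minimum list is only a minimum, and address could identify households while it is held. That narrows the gap to outbreaks and to what survives de-identification.

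Finally, the large losses are extremes. Recruitment also draws on GP practices and inpatients, so many cases will be sporadic. A Clopper-Pearson interval is more forgiving: at m = 5 and ICC 0.1 with every positive clustered, its coverage is about 93%. All of this stands, and it is why the conclusion is conditional.

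**Conclusion.** The point holds as a conditional one. Enrolling linked people is part of the main recruitment strategy, and nothing in the stated analysis, sample size or minimum dataset provides for it. Simple binomial intervals may therefore be too narrow. It would go too far to say that they will be: the documents give neither cluster size nor ICC, and with small clusters or an ICC near zero the loss is negligible.

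Under the assumptions shown, sensitivity coverage runs from no loss down to about 80% in an extreme setting, with about 93% in a plausible mix of sporadic and clustered cases. PPV and NPV are the firmer part of the concern. They need no correlation in swab errors, and PPV coverage falls from about 93% to 79% as outbreaks grow. The point estimates from the 2x2 tables are not in question; the stated precision is.

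**What to change.** - Add a de-identified outbreak/household ID to Minimum data requirements, and state under Deidentification methods that it is kept in the analysis file. Assign it for anyone already enrolled while the linking details are still held.
- State that intervals for sensitivity, specificity, PPV and NPV come from a cluster bootstrap or an intercept-only GEE logistic model with robust variance, with sporadic cases as clusters of one. Use a small-sample correction if there are few clusters.
- Use the same clustering in the logistic regression under Statistical methods.
- State whether one participant may contribute more than one pair. Cluster on person only if so.

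The cost is one data field, a few lines of code and somewhat wider intervals. If clustering proves negligible, the intervals will barely change.

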### Laboratory testing

Faeces will be collected in standard collection containers and rectal swabs utilised will be dry cotton swabs. Samples will be registered and transported chilled using existing referral pathways. Biological materials will be stored in the laboratory in accordance with NPAAC minimum requirements and will be discarded once all required testing on these samples has been completed for assay validation, research and testing required for public health and/or clinical investigations. Faeces and rectal swabs samples will be subjected to nucleic acid extraction using the QIAGEN EZ or KingFisher FLEX instruments. Real-time RT-PCR will be performed to identify hepatitis A or E virus-positive specimens, using existing methods at the Public Health Virology laboratory, Queensland Health. Extracted RNA from hepatitis A or E virus RT-PCR positive samples will then be used to perform partial or whole genome sequencing. Paired rectal swabs and faeces samples from individual patients will be sequenced in parallel on the same sequencing run, using either Nanopore or Illumina sequencing chemistries and instruments. The partial or whole genome sequences generated from each patient will be analysed and firstly aligning with references sequences to determine genotype and then their nucleotide homology and phylogenetic relatedness will be compared to determine whether variation between the sequences from each respective sample type (i.e., faeces vs rectal swab) exists.

### Data collection and management

Laboratory diagnostics will provide the majority of the outcomes using established testing methods. Pathologists will provide the diagnosis for samples. We will be collecting information about demographics, symptomatology, setting it was collected in, type of collect (self-collect vs clinician collect), and two patient reported outcomes by firstly asking the patient if they had an adverse event during or after the testing, and the nature of the event if present. Secondly, we will ask the patient which test they preferred and follow-up with why. Data analysis will be conducted by members of the research team.

Participant-level dataset will not be publicly accessible. Statistical code and full protocol will be publicly accessible.

#### Data storage, access, and de-identification.

This study will collect data related to routine clinical practice (bulk faeces testing), as well as research data (rectal swab results). The results of these tests will be kept in a clinical database (AUSLAB, within Pathology Queensland) as well as within local study databases (Excel spreadsheets or Redcap Databases) for operational and analytical purposes. At all times, data will be kept within Queensland Health databases and will not be shared with external entities. Only Queensland Health staff (includes Pathology Queensland) will have access to the clinical and research data.

Data will be de-identified prior to proceeding to the statistical analysis in accordance with the HIPAA Australia Privacy Act 1988 and the Australian Privacy Principles (APP) Guidelines, which provide the standard for de-identification of protected health information, the Australian De‐Identification Decision‐Making Framework, and AIHW guidelines for disclosure of secondary use health information and the Australian Privacy Act and Australian Privacy Principles [21–24].

#### Minimum data requirements.

At a minimum, data collected for each participant should include:

Identifiers (name, address, date of birth, contact details, comorbidities)Recruitment details (date of recruitment, date of consent, proof of consent, date that test packs were posted, symptomatology, duration of symptoms, presence of blood in faeces (if applicable))Sample collection details (where samples were collected (e.g., at home), who collected the sample (e.g., self-collect), date and time each sample was collected, date samples were submitted to pathology lab)Bulk faeces and rectal swab test results (date that lab testing was conducted for each sample, presence of visible faeces for the rectal swab only, positive/negative detection results for each sample)Follow-up information (date of follow-up attempts, which sample was collected first as reported by the participant, rough estimate of time difference between samples collected, adverse event details, preferred sample method)

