### Study setting

The study aims to recruit patients in the community (primary care or public health responses) and in public hospitals. The mode of collection will either be a self-collect rectal swab (done by the patient themselves) and bulk faeces sample or clinician collect rectal swab and bulk faeces sample within a clinical environment. The generalisability of this trial is supported by its relatively broad inclusion and exclusion criteria, which are designed to reflect routine clinical practice. Because the trial aims to evaluate the use of rectal swabs as an alternative to bulk faeces sampling, eligibility is not restricted (e.g., based on symptom presentation), allowing for the inclusion of participants with diverse clinical profiles. This inclusive approach will mimic routine clinical practice, and facilitate recruitment across a broad range of demographic, clinical, and socioeconomic backgrounds, enhancing the external validity of the findings. Vulnerable groups, such as comorbid or immunocompromised individuals, are identified in the recruitment phase and this data is recorded to be used in the analyses. The lower age limit of 18 years has been set due to ethical and regulatory considerations in recruiting children and performing rectal swabs on a vulnerable group. While children are not included in this study, the trial findings relevant to rectal swab accuracy are expected to be applicable to all ages.

Inclusion criteria:

Persons aged 18 and older.Able to consent to and perform the additional rectal swab test.Close contact or person exposed, suspected, or confirmed case associated with an outbreak of an enteric organism. E.g., hepatitis A outbreak, foodborne outbreak.Chronic carrier of an enteric organism that requires testing.Person involved in a clinical encounter where they are or are likely suffering from a disease caused by an enteric organism. (E.g., person presenting to the GP or Emergency Department with diarrhoea or jaundice)

Exclusion criteria:

Persons unlikely (as judged by the clinician) to be harbouring an enteric organism.Persons where collection of a rectal swab is medically contra-indicated.

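### The blood covariate has no sample-level source among the listed data items, and for posted or delayed kits symptom status and duration are listed only as recruitment items that can be out of date at collection

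*Protocol article*

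**What the plan says.** The section on minimum data requirements in the protocol article groups its items by stage.

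- **Recruitment details** hold the dates of recruitment, consent and pack posting, then "symptomatology, duration of symptoms, presence of blood in faeces (if applicable".
- **Sample collection details** hold the place, the collector, and "date and time each sample was collected, date samples were submitted to pathology lab".
- **Test results** hold the testing date and "presence of visible faeces for the rectal swab only, positive/negative detection results for each sample".
- **Follow-up information** holds contact attempts, which sample came first, and "rough estimate of time difference between samples collected, adverse event details, preferred sample method".

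The scripted questions under Follow-up cover sample order, adverse events and preference. They do not ask about symptoms or blood.

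Statistical methods then lists the covariates for the logistic models of accuracy. The list ends with "symptomatology (symptomatic/asymptomatic), duration of symptoms, and whether blood was present in the sample".

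On timing, the Consent section has telephone consent first and the pack sent afterwards. Under Recruitment, the coordinator can "send sample collection packs to the patient, family, and/or symptomatic members of an outbreak via express post". The eligible population includes any "Close contact or person exposed, suspected, or confirmed case associated with an outbreak of an enteric organism". Missing data allows a replacement kit for someone who has not returned the swab. Study setting and Consent also allow collection in a clinical environment with staff present.

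**The concern.** A covariate meant to explain whether the swab agrees with the stool should describe the participant and the sample when the sample was taken. Two things in the plan work against that.

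First, the model names blood in the sample, while the only blood item is a recruitment detail about faeces in general. For a posted kit that answer describes an earlier stool.

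Second, the people in outbreak work are those whose status is likely to change over a few days. An exposed contact who is well at the call may be ill when the swab is taken, and a case may have recovered. If the recruitment entry is carried forward, such people sit in the wrong symptom category.

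The Introduction says swabs are intended to replace bulk faeces, including for mass testing after outbreaks. Whether accuracy holds in people without symptoms bears on that use. Misplaced symptom status would tend to make accuracy look less dependent on symptoms than it is.

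**Working it through.** The plan gives no figure on this point to reproduce. The check is mainly a comparison of the listed items with the model.

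**Step 1. Trace each covariate to a source.**

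| Covariate in the model | Recruitment item | Sample-collection item | Laboratory item | Follow-up item |
|---|---|---|---|---|
| Symptomatic or not | yes | none | none | none |
| Duration of symptoms | yes | none | none | none |
| Blood in the sample | blood in faeces | none | none (visible faeces on the swab only) | none |

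Only blood is worded in the model as a feature of the sample, and it has no sample-level item. Blood in the collected sample can also arise after recruitment: Risks and harm mentions minimal bleeding from swabbing, and Collection process prefers the swab first.

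**Step 2. Establish whether there is a lag.** With telephone consent and a posted kit, recruitment precedes collection by at least the postal time plus the wait for a bowel motion. No interval is stated. The 24-hour limit in the Abstract concerns the gap between swab and stool, so it does not bound this lag. Where recruitment and collection happen at one visit, the lag can be nil.

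**Step 3. See what can be recovered from the recorded dates.** The recruitment date and the date of each sample are both listed, so

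duration at collection = recorded duration + (collection date − recruitment date).

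For someone recruited on illness day 2 who collects on day 5, this gives 2 + (5 − 2) = 5 days. It is right only if symptoms lasted to collection. If they had resolved, it overstates duration. If the person became ill after the call, there is no onset date to start from. Symptom status and blood at collection cannot be derived from any listed item.

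**Step 4. Show the direction of the effect, on assumed figures.** Let sensitivity be S1 in people symptomatic at collection and S0 in people asymptomatic at collection. Let a and b be the fractions of the recorded symptomatic and recorded asymptomatic groups whose status has changed by collection. If the change is unrelated to the swab result given true status,

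recorded difference = (S1 − S0) × (1 − a − b).

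None of the following inputs comes from the protocol. Take S1 = 97% and S0 = 85%, a true difference of 12 points.

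- a = b = 0: the difference stays at 12 points.
- a = b = 10%: 0.9 × 97 + 0.1 × 85 = 95.8%, and 0.9 × 85 + 0.1 × 97 = 86.2%. The difference is 9.6 points.
- a = b = 20%: 0.8 × 97 + 0.2 × 85 = 94.6%, and 0.8 × 85 + 0.2 × 97 = 87.4%. The difference is 7.2 points.

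The fractions a and b refer to each whole recorded group. If in-clinic pairs have no lag, each equals the share of that group collected with a lag times the change rate among them.

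**The case against.** The strongest reply is that Recruitment details is a heading for a group of fields and not a stated time of measurement. The headings are loose (comorbidities sit under identifiers), the list is a minimum, and the full protocol and data form are not shown. Missing data expects gaps in symptom details to be followed up, so entry is not confined to the first call.

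Part of this stands. The article does not prove that collection-day values will go unrecorded. But the groups follow the order of the trial, and every dated item in the recruitment group precedes use of a posted kit. The follow-up described is for missing entries: a complete entry that has gone out of date triggers nothing. The mismatch between the blood covariate and its listed item is visible within the article itself.

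A reader might go further and infer that all three covariates are analysed as properties of the sample, and that they describe the wrong day throughout the trial. The document does not support this. Symptom status and duration are listed with sex, age and comorbidities as potential confounders. Recruitment and collection can coincide in clinic or hospital, and duration can be updated from the recorded dates while symptoms persist. Nor does the document say that an unadjusted recruitment duration will be analysed. The attenuation figures are likewise no forecast, since neither the sensitivities nor the change rates have a source in the plan.

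**Conclusion.** The point holds in a limited form. The blood covariate has no sample-level source among the listed items. For posted or delayed kits, symptom status and duration are listed only as recruitment items and can be out of date at collection.

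The likely consequence is attenuation of any symptom-related difference in the covariate-adjusted model, provided that changes of status are unrelated to the swab result. Its size cannot be calculated from the document, because neither the lag nor the proportion changing status is given. The primary sensitivity, specificity, predictive values and agreement come from 2x2 tables without these covariates and are unaffected. The stated subgroup analysis is by disease type, so it does not depend on symptom status either.

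The change is still worth making before recruitment is far advanced, because symptom status and blood at collection cannot be reliably reconstructed afterwards.

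**What to change.** 1. Keep the recruitment items as they are.
2. Add to the sample collection details the symptom status on the day of collection and the symptom onset date, with an end date if symptoms have resolved. Capture these on the pathology form in the pack or in the existing follow-up call.
3. Compute duration from the onset date to the collection date, or to the end date if symptoms stopped earlier.
4. Record visible blood in the bulk sample at laboratory receipt, beside the existing field for visible faeces on the swab. The sample order already asked for at follow-up will help to interpret blood that may come from the swabbing.
5. State under Statistical methods that the logistic models use these collection-referenced values.

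The cost is a slightly longer form and one extra laboratory tick box, all at contacts that already exist. No visit is added and clinical care does not change.
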